# Study protocol of the CHOiCE trial: a three-armed, randomized, controlled trial of home-based HPV self-sampling for non-participants in an organized cervical cancer screening program

**DOI:** 10.1186/s12885-016-2859-z

**Published:** 2016-11-03

**Keywords:** Self-sampling, Cervical cancer screening, Screening participation, Human papillomavirus testing

## Abstract

**Background:**

The effectiveness of cervical cancer screening programs is challenged by suboptimal participation and coverage. Offering cervico-vaginal self-sampling for human papillomavirus testing (HPV self-sampling) to non-participants can increase screening participation. However, the effect varies substantially among studies, especially depending on the approach used to offer HPV self-sampling. The present trial evaluates the effect on participation in an organized screening program of a HPV self-sampling kit mailed directly to the home of the woman or mailed to the woman’s home on demand only, compared with the standard second reminder for regular screening.

**Methods/design:**

The CHOiCE trial is a parallel, randomized, controlled, open-label trial. It will include 9327 women aged 30–64 years who are living in the Central Denmark Region and who have not participated in cervical cancer screening after an invitation and one reminder. The women will be equally randomized into three arms: 1) Directly mailed a second reminder including a HPV self-sampling kit; 2) Mailed a second reminder offering a HPV self-sampling kit, to be ordered by e-mail, text message, phone, or through a webpage; and 3) Mailed a second reminder for a practitioner-collected sample (control group). The primary outcome will be the proportion of women in the intervention groups who participate by returning their HPV self-sampling kit or have a practitioner-collected sample compared with the proportion of women who have a practitioner-collected sample in the control group at 90 and 180 days after mail out of the second reminders. Per-protocol and intention-to-treat analyses will be performed. The secondary outcome will be the proportion of women with a positive HPV self-collected sample who attend follow-up testing at 30, 60, or 90 days after mail out of the results.

**Discussion:**

The CHOiCE trial will provide strong and important evidence allowing us to determine if and how HPV self-sampling can be used to increase participation in cervical cancer screening. This trial therefore has the potential to improve prevention and reduce the number of deaths caused by cervical cancer.

**Trial registration:**

Current Controlled Trials NCT02680262. Registered 10 February 2016.

## Background

Organized screening programs have reduced cervical cancer incidence and mortality in many western countries [1–3]. Yet, the effectiveness of such programs is challenged by suboptimal participation and coverage [4, 5], and more than half of all invasive cervical cancers are diagnosed among women who are under- or unscreened [6–8]. It is therefore crucial to identify ways to improve screening participation, e.g. by removing existing barriers to regular screening.

In the Danish organized screening program, the overall participation rate, defined as having a screening test within 365 days after an invitation, is currently 65 % [9]. This percentage has been decreasing slightly in recent years [9]. Earlier studies show sociodemographic inequalities in screening participation [10, 11]. Thus, a Danish study identify several barriers to participation, including lack of knowledge about screening and cervical cancer, discomfort during pelvic examinations, fear of cancer, practicalities in private life, and in access to testing facilities [12]. Some of these barriers may be overcome if self-sampling at home is an option which, however, is not currently the case in the Danish screening program.

Recent research advocates the use of high-risk human papillomavirus (hrHPV) testing over cytology because it is more sensitive in detecting cervical intraepithelial neoplasia of grade 2 or worse (CIN2+) and provides better protection against cervical cancer [13, 14]. Furthermore, hrHPV testing enables women to self-sample cervico-vaginal material; self-collected samples have shown sensitivity for detection of CIN2+ that is comparable to that of clinician-collected samples if validated Polymerase Chain Reaction (PCR)-tests are used [15, 16]. Self-sampling also appears to improve screening participation. Hence, a meta-analysis showed that mailing women a test-kit for self-sampling at home, including pre-stamped envelopes for mailing of the sample to a laboratory for HPV testing, increased screening participation compared with women receiving standard invitation for regular screening [17]. The participation rate for women offered self-sampling varies widely among trials, ranging from 10 % [18] to 39 % [19] with a pooled 12.6 % absolute increase in participation compared with standard invitation when self-sampling kits were mailed directly to all women [17].

Three other trials [20–22] used an opt-in approach for offering self-sampling, i.e. women were mailed an invitation to order a kit by phone [21], or by mail [20], or to pick it up at a pharmacy [22]. One of these trials [20] showed a 12.3 % increase in participation among long-term non-participants, but the two other trials [21, 22] showed no positive effect on participation. Moreover, in the pooled analysis, these trials showed only an insignificant 0.2 % participation increase compared with women receiving standard invitations [17]. Thus, more studies are needed to explore the effect and acceptability associated with other more timely and modern opt-in approaches for offering self-sampling (websites, e-mails, and text messages). To our knowledge, no previous studies have evaluated the effect on participation of offering self-sampling, either directly mailed or using timely opt-in procedures as compared with a standard second reminder.

Therefore, in the efforts to reduce barriers to cervical cancer screening and to increase participation, we will conduct a randomized, controlled effectiveness trial to evaluate the effect of two different approaches for offering HPV self-sampling to women who did not participate in the cervical cancer screening program despite an invitation and one reminder.

## Methods

### Trial design

CHOiCE (Cervical HOme-based CancEr screening) is a parallel, randomized, controlled, open-label trial nested into a population-based, organized cervical cancer screening program conducted in the Central Denmark Region. Women who have not participated in cervical cancer screening after an invitation and one reminder will be randomly allocated to one of the following three arms (Fig. 1):mailing of a modified second reminder including the self-sampling kit (intervention group 1)mailing of a modified second reminder informing the women that they can order the kit either by e-mail, text message, phone or through a study webpage (www.hjemme-us.rm.dk) (intervention group 2)mailing of a standard second reminder (control group)

The modified second reminder informs of the opportunity to collect a self-sample if wanted, but also about the opportunity to have a cervical cytology specimen taken at a general practitioner (GP) (usual procedure). The standard second reminder informs the women about the current test opportunity, but contains no information about self-sampling.

**Fig. 1 Fig1:**
[figure not shown]
Randomized controlled trial design overview. GP: general practitioner

### Study setting

Denmark has a total of 5.6 million inhabitants, with 1.5 million women in the target population for cervical cancer screening [9, 23]. Organized cervical cancer screening was introduced in the 1960s in some Danish counties and non-systematically implemented in the rest of the country until nationwide coverage was achieved in the late 1990s [24, 25]. The policy and organization of cervical cancer screening are defined nationally, but the responsibility for running the screening program lies with the regions [26, 27]. Denmark is divided into five regions one of which is the Central Denmark Region (23 % of the Danish population) [23, 26].

Since 2007, women aged 23–49 years have been invited for cervical cancer screening every third year, while women aged 50–64 years are invited every fifth year [26, 27]. Shortly before 3 or 5 years have passed since a woman’s last registered cervical cytology result, she is sent an invitation advising her to book an appointment with a GP for a pelvic examination at which a liquid-based cytology specimen is collected [27]. If the responsible Department of Pathology does not receive a cervical cytology specimen for analysis, up to two reminders will be sent 3 and 6 months after the initial invitation [27]. Women who do not respond to invitations or reminders will receive a new invitation in the next screening round, unless she has declined participation. For women aged 23–59 years, the primary screening test is liquid-based cytology; while an hrHPV-DNA check-out test is recommended for women aged 60–64 years [26, 27]. In the Danish Cervical Cancer Screening Program, all testing is free of charge [26, 27].

Routinely, all cervical cytology results, HPV test results, and histological diagnoses from cervical biopsies as well all other pathology specimens are registered in the national Danish Pathology Data Bank (DPDB) under the woman’s unique Civil Personal Registration (CPR) number [28–30]. The DPDB also keeps track of which women are due to receive invitations and reminders to participate in screening.

In the Central Denmark Region, all samples in the Cervical Cancer Screening Program are analyzed by the Department of Pathology, Randers Regional Hospital. Invitations and reminders are routinely handled by the Department of Public Health Programs, Randers Regional Hospital.

### Participation and randomization

Participants are restricted to women aged 30 to 64 years living in the Central Denmark Region who have not participated in cervical cancer screening after an invitation and one reminder. Women who are younger than 30 years are not included due to the low specificity of HPV DNA tests in younger women [14].

Participants will be identified on a weekly basis in the nationwide DPDB [28, 29]. The eligible women’s unique 10-digit CPR number [30], including birthdate will be extracted as this allows us to follow, e.g. the women in Danish health registers. A CPR number is assigned to every Danish citizen upon birth [30]. Data will be extracted in Excel format and transferred to the REDCap system for storage and automated randomization [31]. Participants will be assigned randomly to the three arms of the trial in a 1:1:1 ratio as per a computer-generated randomization schedule following simple randomization procedures. The CPR number is used for randomization. The nature of the intervention and allocation ratio precludes the masking of the participants and study staff.

### Interventions

Women in intervention group 1 will be mailed a modified second reminder, a leaflet entitled *Facts*, *benefits, and drawbacks about HPV self-sampling* and a self-sampling kit. The leaflet provides information about HPV and cervical cancer including benefits and drawbacks of HPV self-sampling compared with regular screening. The kit includes a brush device (Evelyn Brush, Rovers Medical Devices B.V, Oss, Netherlands), which should be used to collect a cervico-vaginal sample for subsequent hrHPV testing [32], written and drawn instructions on how to obtain and mail the sample, and a pre-stamped return envelope addressed to the Department of Pathology, Randers Regional Hospital, where the hrHPV testing will be performed. The instructions show how the woman should label the brush device with an attached laboratory specimen barcode. The woman is urged to mail the return envelope on the day the sample is taken. Women in intervention group 2 receive the same material as those in intervention group 1, except for the kit, which will be mailed to the women only on demand. Additionally, the leaflet for this group contains information on how to order the kit (by e-mail, text message, phone, or through a study webpage (www.hjemme-us.rm.dk). Women in both intervention groups and in the control group receive the information that they can contact their GP should they wish to have a cervical cytology specimen taken.

### Analysis of samples

All samples will be handled, processed and analyzed at the Department of Pathology, Randers Regional Hospital.

The self-collected samples will be handled using the Cobas® 4800 HPV DNA test (Roche Diagnostics GmBH, Switzerland) according to the manufacturer’s protocols. The test identifies HPV16, HPV18 and 12 other hrHPV types (31, 33, 35, 39, 45, 51, 52, 56, 58, 59, 66 and 68) in a single pool. Results are either 1) hrHPV-negative, 2) hrHPV-positive (HPV16, HPV18 and/or other hrHPV types), or 3) unsatisfactory. An unsatisfactory result includes specimens with a negative β-globin result, a sample damaged in transit, incorrect labelling, or insufficient material for analysis. The hrHPV test results of the self-collected samples will be registered in the DPDB.

Cervical cytology specimens obtained by GPs will be analyzed using the standard procedure used in the Central Denmark Region, i.e. microscopy as the primary procedure for control group women aged 23–59 years [27]. In case of detection of Atypical Squamous Cells of Undetermined Significance (ASC-US) among women aged ≥ 30 years, an HPV DNA analysis will be performed using Cobas 4800 [9, 27]. For women aged 60–64 years, the primary analysis of the cervical cytology is Cobas 4800 HPV DNA analysis, and microscopy will be used as triage in case of hrHPV-positive test results [9, 27]. When cervical cytology is made as follow-up on hrHPV-positive test results following self-sampling (see below), the specimens will be analyzed by microscopy.

### Follow up after self-sampling

Women tested by use of self-sampling receive a written test result by ordinary mail. Approximately 98 % of all residents in Denmark are listed with a GP [33]. The GP will also be informed of the testing and the test result. Women with an hrHPV-positive test results are recommended to visit their GP for a cervical cytology specimen within 30 days; and hereafter they will be handled as described in Danish routine guidelines [27]. Women with an hrHPV-negative test result will be referred back to the national screening program and recommended to participate in the next screening round. Women with an unsatisfactory sample will receive a second self-sampling kit and will be encouraged to repeat self-sampling at home or to visit a GP for a cervical cytology specimen.

### Sample size

The sample size was determined by the primary objective (comparison of participation in the intervention and control groups, respectively) and women will be allocated in equal numbers to the three randomization groups. Our assumption about participation in the control group (women who have a cervical cytology specimen within 90 days after receiving the standard second reminder) is 28.7 % [34]. A power calculation (considering a 2.5 % significance level and 80 % power) based on finding an expected difference of 3.6 % [35] in participation between the intervention groups and the control group shows that the trial will achieve a statistical power of 80 % if 3109 women are included in each group (a total of 9327 women).

### Data sources and statistical analysis

The DPDB will be used to retrieve data on the CPR numbers of the study population; participation (yes/no); if participation was by self-sampling or by visiting a GP; the hrHPV test results of the self-collected samples, results of cervical cytology specimens, results of cervical biopsies and whether appropriate follow-up was conducted (only for self-sampling women). Furthermore, data on the women’s previous screening history will be obtained from the DPDB. From Statistics Denmark, information on sociodemographic status will be obtained using the women’s CPR number. An overview of the used data sources and information is seen in Table 1.

The characteristics of the women in the intervention groups and the control group will accordingly be presented using descriptive statistics (mean, standard deviation, numbers, or proportions) on sociodemographic factors (e.g. age, marital status, education level, ethnicity, income, living in rural or urban area, and occupation) and previous screening history in order to determine if the randomization was adequately balanced.

Participation will be defined as a submitted self-collected sample or having a cervical cytology specimen within 90 and 180 days after the mailing of second reminders. The proportion of women participating in each group will be calculated, as will the absolute difference in the participation proportion between the control and intervention groups and the corresponding 95 % confidence intervals (CIs). The relative risks and 95 % CIs of having a sample in the intervention groups compared with the control group will be estimated. Per-protocol and intention-to-treat analyses will be performed. The latter include data on women who were invited to self-sample, but instead attended regular screening. Participation will also be reported by age and screening history. The prevalence of hrHPV cases and histologically confirmed CIN lesions in the interventions groups will be reported. Estimates and 95 % CIs of the proportion of women with a hrHPV sample who have appropriate follow-up will also be calculated. Appropriate follow-up will be defined as having a cervical cytology specimen taken at 30, 60, or 90 days after mailing of the test result.

**Table 1 Tab1:** Overview of data sources and information

Data sources	Information
Danish Pathology Data Bank (DPDB)	Participation (yes/no)
	Participation by self-sampling or visiting a GP
	HrHPV test results of self-collected samples
	Dysplasia and/or hrHPV test results of cervical cytology and histology specimens obtained in the whole country
	Screening history
	Age at date of second reminder
Statistic Denmark	Marital status
	Living in rural or urban area
	Education level
	Ethnicity (country of birth)
	Occupation
	Income

All data are registered and collected by use of the unique CPR number which includes the participant’s date of birth

*CPR* Civil Personal Registration, *GP* General Practitioner

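### The primary comparison is described without covariates after simple randomisation; prespecified adjustment for age and screening history would gain some precision at almost no cost

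*Protocol article*

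**What the plan says.** All references are to the Methods of the protocol article unless stated otherwise.

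- **Allocation** (Participation and randomization): women are assigned "in a 1:1:1 ratio as per a computer-generated randomization schedule following simple randomization procedures". No stratification factor is named.
- **Primary comparison** (Data sources and statistical analysis): the participation proportion per arm, the absolute difference from control and the relative risk, with 95% confidence intervals. No covariate is mentioned for any of them.
- **Baseline factors** (same section): age, other sociodemographic factors and screening history are summarised by arm "in order to determine if the randomization was adequately balanced".
- **Other uses of the same factors**: the section also plans to report participation by age and by screening history. The Discussion uses screening history to judge whether self-sampling reaches under-screened or unscreened women.
- **Availability**: data on women's "previous screening history will be obtained from the DPDB", and Table 1 lists age at the date of the second reminder under the same source.
- **Sample size**: control participation "within 90 days after receiving the standard second reminder) is 28.7" percent, a calculation "based on finding an expected difference of 3.6" percentage points, "considering a 2.5 % significance level and 80 % power", met "if 3109 women are included in each group (a total of 9327 women".

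**The concern.** Age and screening history are fixed before the second reminder is mailed and are held in the register from which the women are identified. If they predict who attends, a comparison that ignores them leaves explainable outcome variation in the standard error. Simple randomisation does nothing at the design stage to balance them, so the analysis is the only place where that variation can be removed.

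A second, smaller point is the stated purpose of the baseline table. If a computer-generated allocation is carried out correctly, any baseline difference is chance. The table therefore describes the arms and does not test whether randomisation worked. The article also does not say what would follow if the arms looked unbalanced. Fixing the adjustment set in advance makes that question irrelevant to the main estimate.

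At stake is the width of the intervals and a few points of power at most. The validity of the comparison is not in question.

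**Working it through.** **Inputs from the Sample size section:** p1 = 0.287 (control), difference 0.036, so p2 = 0.323; significance level 2.5%; power 80%; 3109 per arm. The section does not say whether the test is one- or two-sided.

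**Step 1. Reproduce the planned size.** With the pooled-variance formula for two proportions, without continuity correction:

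n = [z(α)·√(2·p̄·(1−p̄)) + z(β)·√(p1(1−p1) + p2(1−p2))]² / (p2−p1)²

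Here p̄ = 0.305, z(α) = 2.2414 (two-sided 2.5%) and z(β) = 0.8416. The two square roots are 0.65111 and 0.65062.

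n = (2.2414 × 0.65111 + 0.8416 × 0.65062)² / 0.036² = 3108.01, which rounds up to **3109**.

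The planned figure is reproduced exactly. Read as one-sided 2.5%, the same formula gives 2567, so the calculation was two-sided. The size is that of an unadjusted comparison, and such a comparison has 80.0% power.

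**Step 2. Precision without adjustment.**

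SE = √[(0.287 × 0.713 + 0.323 × 0.677) / 3109] = √(0.423302 / 3109) = 0.01167, or 1.17 percentage points.

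95% half-width = 1.96 × 1.167 = 2.29 points.

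**Step 3. Precision with adjustment.** Let R² be the share of outcome variance explained by age and screening history. To a good approximation the variance of the risk difference is multiplied by (1 − R²), the half-width by √(1 − R²), and the effective arm size becomes 3109/(1 − R²). The documents give no R², so the values below are assumptions.

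| Assumed R² | Effective n per arm | Power (two-sided 2.5%) | 95% half-width (points) |
|---|---|---|---|
| 0 (unadjusted) | 3109 | 80.0% | 2.29 |
| 0.01 | 3140 | 80.4% | 2.28 |
| 0.03 | 3205 | 81.3% | 2.25 |
| 0.05 | 3273 | 82.2% | 2.23 |
| 0.10 | 3454 | 84.4% | 2.17 |

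At R² = 0.10 the gain equals about 345 more women per arm (3454 − 3109). At R² = 0.01 it equals about 31.

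**Step 4. What such an R² would mean.** For two equal strata, R² = 0.25 × (difference in participation)² / (0.287 × 0.713). Assumed rates of 18.7% and 38.7%, which average 28.7%, give 0.25 × 0.20² / 0.2046 = 0.049. Rates of 23.7% and 33.7% give 0.25 × 0.10² / 0.2046 = 0.012. The assumed range therefore covers weak to moderate prediction.

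**Step 5. Size of chance imbalance.** For a factor present in half the women, the between-arm difference has SD √(2 × 0.25 / 3109) = 1.27 percentage points. With strata 20 points apart in participation (assumption), an imbalance of one SD moves the contrast by 0.0127 × 20 = 0.25 points, against an SE of 1.17 points.

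**The case against.** The strongest case against raising this has four parts.

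1. *The covariate set may sit in a full analysis plan that is not shown.* This is fair. The article does not call its estimates crude and does not exclude adjustment. What stands is that the comparison it describes contains no covariate, so the suggestion is addressed to that description.
2. *Nothing is wrong with an unadjusted comparison.* Correct. It is unbiased under randomisation, it agrees with the sample-size calculation, and its standard error already covers chance imbalance, which Step 5 shows to be small. The point is therefore one of efficiency.
3. *The gain rests on an assumed R².* Also correct. All the women have already passed over an invitation and a reminder, and in such a selected group these factors may predict less well. At the low end the gain is 0.4 points of power.
4. *A baseline table is routine and useful.* It is. Data pass from the register through a spreadsheet into the allocation system, and a table by arm can expose a gross error in that chain. It should stay, and only its stated purpose needs softening.

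Three stronger readings are tempting, and the documents support none of them. A reader might infer that age and screening history serve only to check balance, but participation is to be reported by both, and the Discussion gives screening history a further use. A reader might infer that the trial will adjust after seeing an imbalance, but no passage plans this. A reader might take 80.0% power as a shortfall, but 80% was the target and it is met.

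**Conclusion.** The point holds as an optional improvement. The described primary comparison omits two baseline factors that the trial will hold in any case, under a design that does not stratify on them. Using them in a prespecified way keeps the same marginal risk difference and relative risk and can only be expected to help precision in a trial of this size.

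The gain is modest and of unknown size: 0.4 to 4.4 points of power and 0.01 to 0.12 points of half-width for an assumed R² of 0.01 to 0.10. This rests on the planning rates of 28.7% and 32.3%, a two-sided 2.5% test, covariate data that are complete for the women randomised, and the (1 − R²) approximation. If the covariates predict almost nothing, almost nothing is gained and nothing material is lost.

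**What to change.** - State in advance that the primary estimates are a standardised (marginal) risk difference and relative risk from a logistic model with arm, age at second reminder and DPDB screening history, with robust or delta-method confidence intervals.
- State that this model is used whatever the baseline table shows.
- Keep the unadjusted difference and relative risk as a sensitivity analysis.
- Describe the baseline table as a description of the arms, and drop the aim of determining whether randomisation was balanced.

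The sample size need not change. The covariates are register data that the trial already plans to obtain, so the cost is a few sentences in the plan and a little more analysis code. If a full analysis plan already specifies such a model, only the baseline-table wording remains to be changed.

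### The trial is sized at a two-sided 2.5% level per comparison, but the stated analysis gives only 95% confidence intervals for the two primary comparisons, so the sizing level is not carried forward

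*Protocol article*

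**What the plan says.** Two sections of the protocol article bear on this point.

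- **Sample size.** The calculation is made "considering a 2.5 % significance level and 80 % power". Control participation is assumed for "women who have a cervical cytology specimen within 90 days after receiving the standard second reminder) is 28.7" percent, and the calculation is "based on finding an expected difference of 3.6 % [35] in participation between the intervention groups and the control group". The result is 80% power "if 3109 women are included in each group (a total of 9327 women". The article says neither whether the 2.5% is one- or two-sided nor why 2.5% was chosen.
- **Data sources and statistical analysis.** Participation is to be compared through "the absolute difference in the participation proportion between the control and intervention groups and the corresponding 95" percent confidence intervals, and relative risks against control also get 95% intervals. No test level, 97.5% interval or multiplicity adjustment is mentioned.

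The Participation and randomization section sets equal allocation to three arms, so both interventions are compared with the same control group.

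**The concern.** A significance level in a sample size calculation normally announces the level at which the comparison will be judged. Here the trial is sized at 2.5%, but the next mention of inference for the same two comparisons is a 95% interval, which corresponds to a two-sided 5% level for each. Readers will naturally judge each arm by whether its interval excludes no difference.

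What is at stake is the overall error rate across the two interventions, and whether the stated 80% power describes the inference that will be reported. A borderline result is not far-fetched. The expected gain is only 3.6 percentage points, and the Background section cites a pooled gain of 0.2 percentage points for earlier opt-in trials. If the level is left open, it could also be settled after the results are known.

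**Working it through.** **Inputs, from the Sample size section:** control proportion p1 = 0.287; difference d = 0.036, so p2 = 0.323; power 80% (z = 0.8416); stated n = 3109 per arm. The mean proportion is 0.305.

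**1. Reproduce 3109.** Pooled two-proportion formula without continuity correction:

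n = [z_α √(2 × 0.305 × 0.695) + z_β √(0.287 × 0.713 + 0.323 × 0.677)]² / 0.036²

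The two square roots are √0.42395 = 0.6511 and √0.42330 = 0.6506.

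- Two-sided 2.5% (z_α = 2.2414): (1.4594 + 0.5476)² / 0.001296 = 3108.01, rounded up to **3109**. This is an exact match.
- Two-sided 5%, which is the same as one-sided 2.5% (z_α = 1.9600): (1.2762 + 0.5476)² / 0.001296 = 2566.4, rounded up to **2567**. This is 542 fewer per arm, about 17% lower.

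Other formulas at two-sided 2.5% come close: about 3105 unpooled, about 3107 arcsine, and 3164 with continuity correction. None reaches 3109 at two-sided 5%: 2564 unpooled, 2566 arcsine, 2622 with continuity correction. The 2.5% is therefore not the one-sided half of a two-sided 5% test, which would have agreed with 95% intervals.

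**2. Power at 3109 per arm.** Power = Φ[(0.036 √3109 − z_α × 0.6511) / 0.6506], with 0.036 √3109 = 2.0073.

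- Two-sided 2.5%: Φ(0.842) = 80.0%.
- Two-sided 5%: Φ(1.124) = 86.9%.

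**3. Family-wise error for two comparisons with one control.** With equal arms and no true effects, the two test statistics have correlation 0.5. From the bivariate normal distribution:

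| Rule | At least one false finding in either direction | At least one approach falsely declared effective |
|---|---|---|
| 95% intervals | 9.1% | 4.5% |
| 97.5% intervals | 4.6% | 2.3% |

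If the comparisons were independent, the two-sided figures would be 1 − 0.95² = 9.75% and 1 − 0.975² = 4.94%.

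**4. Where the verdict changes.** The standard error of a difference at the planning rates is √(0.42330 / 3109) = 0.01167. The half-widths are:

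- 95%: 1.960 × 0.01167 = 2.29 percentage points;
- 97.5%: 2.2414 × 0.01167 = 2.62 percentage points.

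The two rules disagree only for observed gains between about 2.3 and 2.6 points (or losses of the same size). The chance of an observed gain in that band is about 7% per comparison if the true gain is 3.6 points, and about 1.2% if there is no effect. The width ratio is 2.2414 / 1.960 = 1.14.

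**The case against.** The strongest defence is that the two sections do different jobs. One fixes a level for sizing and the other a reporting format. The analysis section names no hypothesis test, no p-value threshold and no rule that an interval excluding zero means success. It also uses 95% intervals for the follow-up proportion, which has no comparator, so 95% may simply be a general reporting convention. Reporting 95% intervals while judging significance at 2.5% would be coherent, and a separate analysis plan that is not shown may set the level.

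Much of this stands. A reader might infer that each arm will be judged at 5%, but the article does not say so, and the error rates above apply only under that condition. A reader might also take the 2.5% to be a stated Bonferroni split of 5%. That is the likely reason with two interventions and one control, but the article never gives it.

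The defence does not remove the point. The article is not silent on the level: it gives 2.5% in one section and then, for the same comparisons, only 95% intervals as inference. The alternative defence, that the 2.5% is one-sided and so already matches a 95% interval, fails because that reading gives 2567 and not 3109.

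**Conclusion.** The point holds in limited form. The design level is two-sided 2.5% per comparison, as the stated sample size shows, and the stated analysis does not carry it forward. If conclusions were drawn from the 95% intervals, both family-wise error figures would roughly double. This rests on the planning rates, equal arms and a shared control.

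Two stronger readings are not supported:

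- The 9.1% is not the chance of wrongly declaring an approach effective. It counts errors in both directions; the chance of a false claim of benefit is about 4.5%, against 2.3%.
- The trial is not wrongly sized or underpowered. The 3109 is correct, and judging at 5% would raise power to 87%.

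Because no decision rule is stated and the rules disagree only over a band of about 0.3 percentage points of observed gain, this is something that should be fixed, not something that must be.

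**What to change.** 1. In the analysis section, state that conclusions for the two primary comparisons with control rest on 97.5% confidence intervals (two-sided alpha 0.025 each), and that any 95% intervals for them are descriptive.
2. In the Sample size section, state that the 2.5% is two-sided per comparison and, if that was the intention, that it is a Bonferroni split of 5% over the two comparisons.

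The cost is wording. The primary intervals become about 14% wider (half-width 2.62 instead of 2.29 percentage points at the planning rates). The 3109 women per arm already cover this, with 80% power per comparison and a two-sided family-wise error of about 4.6%.
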